### Trial procedures

Once participants meeting inclusion criteria have provided informed consent to participate, one of two study researchers will collect data indicating participant characteristics and will undertake baseline assessments. Stratification factors will be entered into the concealed online randomization system by the study researchers, who will inform the artists of group allocation. Participants in the intervention group will be invited to attend one individual and one group intervention session per week with the artist, for up to a maximum of eight sessions. The art portfolios will be delivered to participants allocated to the control group after baseline assessment.

A third researcher, blinded to group allocation and trained to administer outcome measures, will undertake outcome assessment with participants in the intervention group after eight art sessions, or at hospital discharge, if that occurs beforehand. The blinded researcher will undertake outcome measures with the control group at four weeks, or at discharge if that occurs prior to four weeks. Participants will be instructed not to reveal their group allocation to this researcher, but any episodes of un-blinding will be recorded. Three months after outcome assessment, the researcher will contact participants to arrange a follow-up assessment, which will be conducted in hospital or at the participants’ home, depending on discharge status. Nine participants from the intervention group and three from the control group, purposefully selected to reflect age, disability and gender, will also be invited to participate in audio-recorded in-depth interviews after follow-up assessment to evaluate their experiences of participation in the CEI, and the trial.

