Artistic goals will be set and jointly reviewed by the artist and the participant at each of the intervention stages, and the processes of art-making and the nature of the finished product will be tailored according to progress. To achieve goals, each participant will receive a maximum of four group and four one-to-one sessions with the artist. Group sessions were selected because the social benefits of group interaction during art have previously been shown to be effective [25, 27]. There is also evidence that one-to one sessions with the artist are beneficial for engagement [26]. For these reasons, both modes of delivery will be selected. Participants will engage with the artist over three to five weeks to a maximum of eight sessions. This duration was selected as it reflects the average length of stay of stroke patients in these rehabilitation centers. Participants will have the opportunity to attend at least two sessions per week. The individual sessions will last up to one hour and the group session will last up to one hour and 30 minutes.

During these sessions participants will be progressively taken through the five intervention stages, within which activities and art materials will be adapted and artwork progressed according to personal interests and abilities. Participants may repeat one or more stages a number of times during the course of the intervention duration. When the participant achieves stage 5 in the intervention the artist will review that work and negotiate with the participant to agree at which of the five stages the participant would like to next engage. This may be stage 2 (exploring different materials), stage 3 (developing a new idea or theme) or stage 4 (further work based around an already established idea or theme).

The artists will monitor participants’ progress closely throughout the trial and complete a sessional log of progress, events, material use and other pertinent observations. This log will be reviewed on a monthly basis to establish if any intervention modifications are required. The completion of study documentation will also be monitored on an ongoing basis by the research manager and research associate and will be assessed and reported at the end of the study.

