The intervention will take place within two inpatient stroke rehabilitation units at a large wheelchair accessible table(s) in an appropriate location not used for other rehabilitation activity or therapy. All equipment utilized will also be appropriate to this setting (table-top easel, cutting mat and so on). Sessions will be delivered face-to-face by the trained artist as one-to-one sessions with individual participants, between Monday and Friday. To ensure that art participation does not encroach on individual rehabilitation therapies (physiotherapy, occupational therapy and speech and language therapy), which are delivered Monday to Friday, the group sessions with up to a maximum of five participants, will be convened at the weekend, depending on recruitment rates.

The intervention is in addition to usual rehabilitation. Usual rehabilitation includes, depending on need, half an hour per day of physiotherapy, occupational therapy and speech and language therapy. The intervention protocol is included as Additional file 1. At the end of the study, participants will be provided with details of community programs that people with stroke can attend after hospital discharge. When reporting study findings for publication, we will follow the Template for Intervention Description and Replication (TIDieR) checklist [37].

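### The post-intervention assessment is timed by attendance in one arm and by calendar in the other, so elapsed recovery time can differ between arms, in either direction

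*Protocol article*

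**What the plan says.** The Trial procedures section of the protocol article gives the two arms different triggers for the first outcome assessment. In the intervention arm the blinded researcher "will undertake outcome assessment with participants in the intervention group after eight art sessions, or at hospital discharge, if that occurs beforehand". For controls the same researcher "will undertake outcome measures with the control group at four weeks, or at discharge if that occurs prior to four weeks". The article states no calendar limit for an intervention participant who stays in the unit without reaching eight sessions, and it does not say from what date the control arm's four weeks run.

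The pace of the intervention is described in three places. Trial procedures says that participants are "invited to attend one individual and one group intervention session per week with the artist, for up to a maximum of eight sessions". Intervention procedures says "Participants will engage with the artist over three to five weeks to a maximum of eight sessions" and also "Participants will have the opportunity to attend at least two sessions per week". The same section adds that group sessions "will be convened at the weekend, depending on recruitment rates".

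The later visit inherits the timing of the first: "Three months after outcome assessment, the researcher will contact participants to arrange a follow-up assessment".

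**The concern.** One rule counts sessions attended and the other counts days. Attendance is observed after randomisation and exists in one arm only, so the time from randomisation to assessment is not comparable by design. The Methods/Design section says that patients typically enter these units less than two weeks after onset. The Stroke Impact Scale, the likely primary outcome, covers strength, mobility, daily living and communication, which may well still be changing at that stage. If one arm is measured later on average, it has had more time to recover, and the difference is read as part of the treatment contrast. If it is measured earlier, the contrast is understated. Because follow-up is counted from the first assessment, the offset carries into the three-month comparison.

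No confirmatory test is at stake. What is at stake are the trial's stated products: effect sizes, the choice of primary outcome for a definitive trial (guided partly by which measure shows the greatest difference), and the power calculation. A timing artefact would be largest on the measures that change fastest.

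A secondary worry is blinding. The stated safeguards are telling participants not to disclose allocation and recording un-blinding. Neither covers what the date of a visit may reveal.

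**Working it through.** **Inputs from the protocol article.** Eight sessions at most; two a week in Trial procedures, two or more a week in Intervention procedures; engagement over three to five weeks; control assessment at four weeks; average stay 35 days; screening within a week of admission; expected stay of at least three weeks for eligibility; 40 per arm. The article gives no alpha, power, effect size or SD, so there is no figure of that kind to reproduce.

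**Step 1: when the rules agree.** Weeks to trigger = 8 / sessions attended per week. At two a week, 8/2 = 4.0 weeks, equal to the control time. Three weeks needs 8/3 = 2.67 a week, and five weeks needs 8/5 = 1.6 a week. Against four weeks, the planned range gives a gap of 3 − 4 = −1 to 5 − 4 = +1 week.

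**Step 2: the mean gap once discharge ends the wait.** I simulated the earlier of eighth session and discharge, against the earlier of day 28 and discharge. The assumptions, none of them in the article, are:
- 70% to 90% of offered sessions attended, each independently;
- stay after enrolment either (a) gamma with mean 28 days (35 − 7) or 35 days and SD 10 or 14, or (b) three weeks plus an exponential tail, with mean four or five weeks.

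| Sessions offered per week | Mean gap, stay (a) | Mean gap, stay (b) |
|---|---|---|
| 2 | +1.0 to +5.3 days | +0.7 to +4.4 days |
| 2.5 | −2.6 to +1.9 days | −2.3 to +1.5 days |
| 2.67 | −3.9 to +0.8 days | −3.6 to +0.5 days |

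Positive means that the intervention arm is assessed later. At two a week with full attendance the gap is 0. At two a week with 70% to 90% attendance, about 25% to 70% of the intervention arm under (a), or 21% to 57% under (b), would be assessed after day 28. Under the rule as written, no control would be. If assessment were in practice forced at five weeks, the largest gaps fall from +5.3 to +3.7 days (a) and from +4.4 to +2.9 days (b).

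**Step 3: from days to SD.** Bias = gap in weeks × recovery slope, with an assumed slope of 0.05 to 0.20 SD per week.
- Half a week: 0.5 × 0.05 = 0.03 to 0.5 × 0.20 = 0.10 SD.
- A full week: 0.05 to 0.20 SD.
- Most extreme late case in the table: 5.3/7 × 0.20 = 0.15 SD; with the five-week limit, 3.7/7 × 0.20 = 0.11 SD.
- Most extreme early case: −3.9/7 × 0.20 = −0.11 SD.
- A middling case: 3/7 × 0.10 = 0.04 SD.

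**Step 4: against random error.** The standard error of a standardised difference with 40 per arm is √(2/40) = 0.224 SD, with a 95% half-width of 1.96 × 0.224 = 0.44 SD. The bias is smaller than this, but a larger sample would not remove it.

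**Step 5: effect on the definitive trial (illustration).** n per arm = 2(1.960 + 1.282)²/d² at 90% power and two-sided 5%. If the true d is 0.30, n = 234. An estimate shifted to 0.40 gives 132, and one shifted to 0.20 gives 526.

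**The case against.** The strongest reply is that the two rules are meant to coincide, and at the planned pace they do. Discharge ends the wait in both arms. With an average stay of 35 days from admission and enrolment about a week in, many participants in each arm would be assessed at discharge whatever their allocation. Missed sessions can be made up where more than two a week are offered. The trial tests no definitive hypothesis, end of intervention is its declared time point, and the choice of primary outcome also weighs relevance and missing data. Visit windows and the use of actual assessment time in the model are details that an article may leave to the full protocol or the analysis plan.

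Most of this stands as a limit on size. It does not remove the asymmetry, which the article states explicitly.

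Two stronger readings are tempting but unsupported. A reader might infer that the intervention arm is always assessed later, so that the bias always favours it. That follows only if two sessions a week is a ceiling. Intervention procedures offers two or more and allows completion in three weeks, and the table in the working then shows gaps of either sign. A reader might also infer that any in-hospital assessment after week four reveals allocation. That requires the assessor to know the enrolment date and controls to be seen exactly on time. The article states neither, other researchers handle consent, baseline and randomisation, and enrolment can be delayed until a patient is medically stable. Timing could hint at allocation; the article does not show that it would.

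**Conclusion.** The concern holds as a design weakness of modest size and uncertain direction. As written, the assessment rules can give the arms unequal time since randomisation at both outcome visits. Under the assumed attendance, stay and slopes, the mean gap is a few days and the resulting bias roughly 0.1 SD or less. It reaches about 0.15 SD only where low attendance, long stay, the steepest slope and no five-week limit coincide. The direction depends on whether sessions run faster or slower than two attended per week.

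The recovery slope is the weakest assumption. The article gives none, and one slope is unlikely to suit both physical function and a measure such as trait hope. The bias is below the random error at 40 per arm, but it is systematic and passes into the estimates on which the next trial would be planned. It should be fixed, and it is not a reason to doubt the recruitment, retention or acceptability results.

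**What to change.** Use one clock in both arms: first outcome assessment four weeks after randomisation, or at discharge if earlier, whatever number of sessions was attended. Count the follow-up visit from randomisation too. Have someone other than the assessor generate visit dates from the randomisation date, so that no attendance trigger reaches the blinded researcher.

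The Study timeline and Trial status sections put the end of recruitment in July or August 2014, so this can no longer change the first assessments. For data collected under the current rule, record the actual assessment dates, report days since randomisation by arm, and add this time to the mixed model as a sensitivity analysis. That is a partial remedy. In the intervention arm the timing depends on attendance, and controls have no planned assessment between week four and follow-up, so the adjustment leans on the assumed shape of recovery. The common clock should be carried into the definitive trial.

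The cost is a sentence of protocol wording, one scheduling rule and one extra model. The small downside is that some intervention participants would be assessed before their eighth session. That fits an intervention defined by a maximum number of sessions and an intention-to-treat analysis. The statements of session frequency in Trial procedures and Intervention procedures should also be reconciled, since they determine how far the current rules diverge.

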### Measures and measurement instruments

Preparatory qualitative work informed the trial design and enabled us to identify the types of outcome likely to be influenced by the CEI. Following on from the qualitative work, discussions with stroke survivors about their perceptions of undertaking the measures and how aphasia-friendly specific measures were, led to the final selection of measures. Outcome measures will be as follows:

#### Stroke-related health status

The Stroke Impact Scale [38] is a 59-item measure examining eight domains of health status: strength, hand function, ADL, mobility, communication, emotions, memory and thinking and participation and/or role function. Validity and reliability are established with Cronbach alpha coefficients of between 0.83 and 0.90 each of the eight domains [39–41]. Its’ test-retest reliability is good with intra-class correlation coefficients (ICC) of 0.7 to 0.92, excluding the domain of emotion, in which the correlation was lower (ICC = 0.57). High correlations were also demonstrated with the Mini-Mental State Exam, Barthel Index, Lawton Instrumental Activities of Daily Living, and the Motricity Index. Each item is rated on a five-point Likert scale indicating difficulty in completing the item. Summative scores for each domain range from 0 to 100. An additional question asks for a rating of 1 to 100 to indicate perceived degree of recovery from stroke. Scores can be added to provide a composite disability score.

#### Mood

The Positive and Negative Affect Scale [42] is a 20-item self-report measure comprising 10 positive and 10 negative affective descriptors. Measurement reliability has been examined; for the Positive Affect (PA) Scale, the Cronbach alpha coefficient was 0.86 to 0.90 and for the Negative Affect (NA) Scale it was 0.84 to 0.87 [39]. Over eight weeks the test-retest correlations were 0.47 to 0.68 for the PA and 0.39 to 0.71 for the NA. Strong correlation with measures of general distress and dysfunction, depression and state anxiety have also been reported [39]. Participants are asked to score the items on a five-point scale [1–5] ranging from ‘very slightly or not at all’ to ‘very much or extremely’ to indicate their emotions in the last week. The positive and negative affect scales each have a potential range of 10 to 50, where higher scores indicate higher affect. The scale has high validity and reliability for use in rehabilitation [43].

#### Self-esteem

The Visual Analogue Self-Esteem Scale [44] was designed to measure self-esteem following stroke. Cronbach alpha values between 0.74 and 0.84 have been reported, as have test-retest correlations of 0.80 and above [41]. The scale had concurrent validity with the Rosenberg Self-Esteem Scale (r = 0.74) when used in an aphasic stroke population [45]. The scale consists of 10 pairs of line drawings representing opposing poles of self-descriptive constructs. Written labels above the drawings explain the constructs. Participants are asked to rate the extent to which the constructs reflect perceptions of themselves on a scale ranging from one to five. The item responses are summed to provide a total score ranging from 10 to 50.

#### Recovery locus of control

The Recovery Locus of Control Scale is a nine-item scale designed to measure perceptions of control over recovery [46]. Scale items measure internal and external beliefs. Items are scored on a five-point Likert scale, with no control represented as one and complete control as five. The scores of all items are added to give a measure of the strength of internal control between nine and 45, with 45 indicating maximum internal control. Validity and internal consistency with stroke survivors has been established [46]

#### Hope

The Trait Hope Scale [47] is a 12-item measure that comprises two subscales: a four-item agency subscale (for example, ‘I energetically pursue my goals’) and the four-item pathways subscale (for example, ‘There are lots of ways around any problem’). An additional four items are distracters. Both subscales have good internal reliability, with Cronbach’s alphas ranging from 0.70 to 0.84 for the agency subscale, and from 0.63 to 0.86 for the pathways subscale [47, 48], and has concurrent validity when compared to instruments examining similar psychological constructs, such as optimism and self-efficacy. Items are scored on a four-point Likert scale, using anchors ranging from ‘1 = definitely false’ to ‘4 = definitely true’.

#### General self-efficacy

The General Self-Efficacy Scale [49] is a 10-item scale that is designed to assess optimistic self-beliefs to cope with a variety of difficult demands in life. Cronbach’s alpha values range from 0.76 to 0.90, with the majority of values in the high 0.80s, illustrating good criterion validity. Responses are made on a four-point scale scoring between one and four. Responses are summed to give a total score out of 40, indicating maximum self-efficacy. The scale has been widely used with stroke populations [50, 51].

#### Self-efficacy for art

To assess self-efficacy and perceived difficulty for art expression we will ask two single item questions, generated following an established procedure for examination of self-efficacy [52]. The questions are: 1. How confident are you that you can express yourself through art activities? And 2. How difficult do you find it to express yourself through art activities? Self-efficacy for art expression will be scored on a seven-point vertical visual analogue scale with one as least confident/difficult and seven as most confident/difficult.

### Outcome measures

The proposed outcome measures were selected to reflect clinical and stroke-related outcomes likely to be affected by the intervention. The final selection of primary outcome for a definitive trial will be determined by the findings of this feasibility trial, but our exploratory work indicates that stroke-related health status measured by the Stroke Impact Scale, is likely to the primary outcome measure. The scale examines communication, participation in life roles, physical status and mood, which were key outcomes indicated by the qualitative work as important benefits of art participation. In addition, the Positive and Negative Affect Scale was selected to investigate positive emotions such as enthusiasm and alertness, which our qualitative work and other recent studies [26] indicate might be influenced by art participation. Similarly, the qualitative work demonstrated that stroke survivors perceive improved self-esteem through art participation, but more specifically from the final stage of the intervention, in which the artwork is displayed and viewed by others. We therefore included the Visual Analogue Self-Esteem Scale [45] as an outcome measure.

To examine underlying psychological constructs that appear to explain how art might influence improvements in the above outcomes, we have also included other secondary outcome measures. Participants in the qualitative study indicated these as important. Survivors suggested that recovery of upper limb function and communication occurred because art provided them with the opportunities to develop their own control of these aspects of stroke recovery in ways that other rehabilitation did not. The art itself provided ways in which survivors could use their upper limbs and try out activities for themselves. Interactions with the artists and within the group provided an environment in which survivors could practice and regain control over their communication. We have therefore included as an outcome the recovery locus of control [46], which indicates internal or external locus of control over recovery and will provide a measure of change in control as a result of art participation.

Confidence that personal rehabilitation goals and art-specific goals could be achieved was generated through the opportunities for skill acquisition that art provided. Confidence was inferred by the qualitative study as a route by which art participation improved recovery, self-esteem and mood. We therefore included a measure of general self-efficacy [49–52] and one that examines self-efficacy for art [46], to evaluate whether art improves self-efficacy and influences more distal outcomes, such as stroke recovery. Perceptions of difficulty can also influence self-efficacy therefore a single-item measure to assess difficulty has been included, as suggested by Francis *et al*. [52].

Hope appears to predict better rehabilitation outcomes. Hope occurs when a person perceives routes to achieving goals and has motivation to access those routes [53, 47]. It has been hypothesized that in rehabilitation hope buffers negative emotions because the individual believes that goals can be achieved despite obstacles [48, 54]. Hope was another concept that our qualitative interviews suggested was developed through art participation. We therefore included the Hope Trait Scale [47] as a secondary outcome. The scale measures hope agency thinking, which represents a patient’s wilful sense of determination to meet goals, and pathway, which reflects a patient’s perceived availability of ways to attain a goal.

This is a pilot trial, therefore as well as clinical and psychological outcomes, we are also collecting data on other outcomes that relate to the feasibility of conducting a definitive trial. We will collect data and evaluate trial recruitment rates, the proportion of participants who prefer to be randomized to art and retention and dropout rates. We will examine the variability of scores on outcome measures and completion rates and ease of use of the chosen measuring instruments at each assessment point. We will also undertake comparison between the measures to determine which are more appropriate for use in a definitive trial. Finally, we will evaluate with participants and staff, the acceptability and feasibility of undertaking the trial in rehabilitation settings.

